## Methods/design

### Trial design

This trial will be conducted in compliance with the Australian National Health and Medical Research Council (NHMRC) National Statement on Ethical Conduct in Human Research (2007), the Note for Guidance on Good Clinical Practice (CPMP/ICH-135/95), and the conditions of the ethics approval granted by St Vincent’s Hospital Human Research Ethics Committee (HREC/14/SVH/343). Results for this trial will be reported in accordance with the CONSORT statement.

The protocol for Australian FASHIoN is similar to that for the parallel UK FASHIoN trial [25], and benefits from the feasibility study performed for the UK trial [26, 27] and from collaboration between the Australian and UK research groups. Inclusion and exclusion criteria, and intervention specifications are identical. Patient-reported outcomes and timing of those outcome assessments are the same. The key differences are the mechanistic structural and biomechanical outcomes investigated in the Australian FASHIoN trial.

The Australian FASHIoN trial is a pragmatic, assessor- and statistician-blinded, two-arm superiority RCT with 1:1 allocation ratio. 140 participants will be recruited from the private and/or public clinics of eight orthopaedic surgeons, spread across three regions in Australia. Recruitment and/or arthroscopic surgery will be carried out at the following hospital sites; in New South Wales (NSW): Mater Hospital, Norwest Hospital, Sydney Adventist Hospital, St George Private Hospital, St Luke’s Hospital, Sutherland Hospital; in Victoria (VIC): Maroondah Hospital, St Vincent’s Private Hospital (East Melbourne), Western Health; and in the Australian Capital Territory (ACT): Canberra Hospital, Calvary Hospital. The PHT program will be administered at various private physiotherapy clinics located throughout NSW, VIC and ACT.

PHT will commence after treatment allocation and continue for a maximum of six months, with six compulsory physiotherapy sessions within the first 12 weeks and up to ten sessions over the first six months if needed by the participant. Arthroscopic hip surgery will occur as soon as practicable and no more than 18 weeks after treatment allocation. Post-operative rehabilitation will not be standardised, and will occur as per each participating orthopaedic surgeon’s usual rehabilitation protocol. The primary outcome will be measured 12 months post-randomisation. For further details, see Trial Design flow chart (see Fig. 1).

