### Patient reported outcomes

Patient reported outcomes will be collected at baseline, 6 months, and 12 months, as described in Table 1. The modified World Health Organisation Health and Work Performance Questionnaire (WHO HPQ) [38] will be utilised to assess cost-effectiveness of the interventions. Changes in participant symptoms and quality of life will be assessed using the iHOT-33 [39], the HOOS [40–42], EQ-5D [43] and the SF-12 [44]. A Global Improvement Scale (GIS) will be used to determine patient perceived overall improvement at 6 months and 12 months following baseline. Patient satisfaction will be measured on a five-point Likert scale after 12 months, in response to the questions, *“Overall, how satisfied are you with the treatment you received?”* and *“Overall, how satisfied are you with the results of your treatment?”.*

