The above strategy will also be performed for analysis of other approximately normally distributed secondary outcome measures including those related to plain radiography, MRI, muscle strength, full 3D gait analyses, EMG-informed NMS and FEM models, and the patient reported outcomes (iHOT-33, HOOS, EQ-5D and SF-12). Differences in dichotomous outcome variables such as adverse events, complications related to the trial interventions and the need for further procedures will be compared between groups using chi-squared tests (or Fisher’s exact test). The temporal patterns of complications and the need for further procedures will be presented graphically. If there are sufficient events cumulative incidence curves of the time to first procedure (any or a specific type) will be plotted by treatment group calculated using the Kaplan-Meier method. Ordinal scores for patient satisfaction will be compared between intervention groups using proportional odds logistic regression analysis with the proportional odds assumption checked. Although our inferences will be drawn from the intention-to-treat analysis, we will perform per protocol analyses to place these in context. We plan to perform exploratory subgroup analyses by FAI type and by whether referral to the study was via the private or public healthcare systems. We do not anticipate that crossovers will be a major issue for this study. We, therefore, expect the main analyses to provide definitive results. If participant adherence to or completion of the PHT proves to be more problematic than expected, we will augment the planned analysis with a complier average causal effect (CACE) analysis.

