### Sample size

Sample size calculations for the primary outcome are based on statistical power of 90%, and two-sided significance of 5% significance level. With a sample size of 54 patients in each group, we expect to detect a difference of at least 50 ms between two study groups at 12 months based on a standard deviation (SD) of 80 ms for the dGEMRIC index [65, 66]. 50 ms was chosen as clinically significant based upon increased risk of subsequent total hip replacement [67].

Previous research identified an R^2^ ≈ 0.2–0.3 between indirect external measures of hip joint loading and hip neck bone density in people with hip OA, when two covariates (weight and height) were included, indicating a moderate relationship between biomechanical and structural measures. We expect higher R^2^ values, given that we have direct estimates of cartilage stress and strain. Being conservative, however, in order to achieve an R^2^ > 0.2 between cartilage loading stimulus and dGEMRIC scores (with three covariates), a power of 90%, and a two-sided significance level of 5% we require a total of 56 patients at each site. We will, therefore, aim to recruit a total of 140 participants for the study to allow for a drop-out rate of 20%, including 5% cross over to the surgical group.

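### The questionnaires have follow-ups at 6 and 12 months, but the named analysis is a single-follow-up test of change, so the main 12-month comparison ignores the 6-month score of anyone missing at 12 months

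*Protocol article*

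**What the plan says.** - **Collection.** The Patient reported outcomes section states: "Patient reported outcomes will be collected at baseline, 6 months, and 12 months". Table 1 agrees: iHOT-33, HOOS, SF-12 and EQ-5D appear at all three times, while the dGEMRIC scan appears only at baseline and 12 months.
- **Objective.** The Secondary objectives set the iHOT-33 and SF-12 comparisons at 12 months.
- **Analysis.** For dGEMRIC, the Statistical analysis section compares mean change from baseline to 12 months by an independent-samples t-test, with an adjusted ANCOVA of the same change. It then extends this strategy to other approximately normal secondary outcomes, including "the patient reported outcomes (iHOT-33, HOOS, EQ-5D and SF-12"). No repeated-measures model is named.
- **Missing data.** The Descriptive analysis text allows multiple imputation if it is judged appropriate and uses imputed datasets to gauge sensitivity to missing data. It does not say which variables would enter the imputation.
- **Expected loss.** The Sample size section sets the target of 140 "to allow for a drop-out rate of 20" per cent, a figure that includes 5% crossover to surgery.

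**The concern.** A method built for one follow-up is applied to outcomes with two. At 12 months, both the t-test and the ANCOVA use only participants with a 12-month form. A participant who answered at 6 months and was then lost adds nothing to the contrast, although the 6-month score is the best available evidence of how that participant was doing.

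The completer t-test is unbiased if, within each arm, loss is unrelated to change. The completer ANCOVA is unbiased if loss depends only on arm and baseline. Neither allows for loss that depends on how the participant had responded by 6 months. The Blinding section says that participants cannot be blinded, and the Statistical analysis section foresees possible trouble with completion of the physiotherapy programme. Loss that follows response, and does so differently in the two arms, is therefore plausible. The stake is the 12-month questionnaire comparison, including iHOT-33, which this trial shares with its UK counterpart.

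**Working it through.** **1. The plan's own figure.** Inputs from the Sample size and Trial design sections: "statistical power of 90%, and two-sided significance of 5% significance level"; a difference of 50 ms; SD 80 ms; 1:1 allocation.

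n per arm = 2 × (1.960 + 1.282)² × 80² / 50² = 2 × 10.51 × 2.56 = 53.8, so 54. This matches "With a sample size of 54 patients in each group". Power at 54 is 90.1% (the exact t-test calculation gives 54.8, so 55).

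The target of 140 equals 112 / 0.8, that is 2 × 56 inflated for 20% loss. These figures concern dGEMRIC only, and no power statement is made for the questionnaires. Nothing below alters them.

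**2. Precision.** Let n12 be the number per arm with a 12-month form, n6 the number with a 6-month form (including those lost later), and r the 6-to-12-month correlation given baseline. Then

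variance ratio (model using both visits / 12-month completers) = 1 − r² × (n6 − n12) / n6.

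Take 70 per arm, with n12 = 56 (20% loss). Assumed, not in the protocol: r from 0.4 to 0.8, and half to all of the 14 lost having a 6-month form.

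- Half, r = 0.4: 1 − 0.16 × 7/63 = 0.982; SE 0.9% lower.
- Half, r = 0.6: 1 − 0.36 × 7/63 = 0.960; SE 2.0% lower; effective n = 56 / 0.960 = 58.3.
- All, r = 0.8: 1 − 0.64 × 14/70 = 0.872; SE 6.6% lower; effective n = 64.2.

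If true loss is nearer 15%, because 5 points of the 20% are crossover, the SE reduction is at most 4.9%.

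**3. Bias.** Large simulation (1,000,000 per arm). Assumed, not in the protocol:
- SD of change 22;
- correlation 0.7 between 6- and 12-month scores, and 0.3 to 0.5 between baseline and each follow-up;
- true difference of 6 points at both visits;
- all 6-month forms returned;
- 12-month loss following a logistic model in 6-month change, with log-odds slope 1 per SD unless stated.

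| Loss by 12 months | t-test | ANCOVA | Both visits modelled |
|---|---|---|---|
| Same mechanism, 20% in each arm | 6.0 | 6.0 | 6.0 |
| Same mechanism, 25% physiotherapy v 15% surgery | 4.6 to 4.8 | 5.2 | 6.0 |
| 25% response-related in physiotherapy, 15% random in surgery | 2.3 to 2.7 | 3.9 | 6.0 |
| As the row above, slope 0.5 | 3.9 to 4.2 | 4.8 | 6.0 |

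The t-test results are sensitive to what drives loss. If loss follows the 6-month score itself rather than the change, the second row becomes 5.4 to 5.6 (t-test) and 5.1 to 5.2 (ANCOVA). The third row becomes 4.5 to 5.0 and 3.6 to 3.8. The model using both visits stays at 6.0 in each case.

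**The case against.** The strongest reply is that the protocol does address missing data. Multiple imputation that includes the 6-month score would rest on the same missing-at-random assumption as a mixed model and recover nearly the same information. Imputation predictors are ordinary SAP content, the SAP is not shown, and ANCOVA of change at a fixed time is a standard method that matches the 12-month objective. In part this stands: the absence of an imputation model from an article is no fault. But the article does name the main method for these outcomes, and that method uses one follow-up. Imputation, as worded, is conditional and a check on that analysis, so the headline estimate remains the completers' estimate.

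A reader might infer that the 6-month scores are thrown away. The protocol does not say so: they may be analysed as a time point of their own, or enter an imputation.

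A reader might also infer a severe bias in any plausible case. That does not follow. Bias needs loss that differs between arms in rate or mechanism, and the largest figures need response-related loss in one arm only. Patients dissatisfied after surgery may leave too, and those who cross over are not lost, since they remain in the intention-to-treat comparison. Even in that one-sided case, baseline adjustment keeps the ANCOVA estimate near 3.9 when loss follows change; the estimates of 2.3 to 2.7 belong to the t-test alone.

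**Conclusion.** The point holds, at moderate weight. The stated main analysis of iHOT-33, HOOS, EQ-5D and SF-12 does not use the 6-month score of participants missing at 12 months, and the optional imputation does not secure its use.

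The case rests on bias, not precision. On a true difference of 6 points, the shortfall ranges from nil (same mechanism and rate), through about 0.8 (ANCOVA) and 1.2 to 1.4 (t-test) at 25% v 15% loss with a common mechanism, to about 2.1 (ANCOVA) and 3.3 to 3.7 (t-test) when only physiotherapy-arm loss follows response. These sizes depend on the assumed SD, correlations and loss model, and on complete 6-month returns, none of which the protocol gives. The precision gain is about 1% to 7% of the SE.

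It would be wrong to read this as a weakness in the primary result. dGEMRIC has no 6-month scan, so its analysis and the sample size are untouched.

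**What to change.** For each approximately normal questionnaire score, make the main analysis a repeated-measures mixed model of the 6- and 12-month scores. Include arm-by-visit and baseline-score-by-visit terms, the minimisation factors (study site and FAI type) and an unstructured covariance, and use all randomised participants with any follow-up. Keep the 12-month arm contrast as the stated comparison.

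An equivalent choice is to make multiple imputation the main analysis for these outcomes and to state that the imputation model includes the 6-month score.

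The cost is a sentence or two of analysis wording and slightly more modelling work, with no new data. Either route relies on data being missing at random given arm, baseline and the 6-month score. That is still an assumption, but a weaker one than the completer analysis requires.

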#### Secondary objectives

Compare 12-month change in hip cartilage health between treatment groups, as demonstrated by changes in the dGEMRIC scores of separate acetabular and femoral head cartilage ROIs at the chondrolabral transitional zone.Compare 12-month change in hip MRI and plain X-ray features between treatment groups, using the Hip Osteoarthritis MRI Scoring System (HOAMS) and Hip2Norm software, respectively.Compare 12-month change in hip joint three-dimensional stresses and strains during walking and various functional tasks between treatment groups.Determine if changes in hip joint structure after 12 months are related to symptomatic improvements.Compare 12-month change in hip muscle activation patterns and co-contraction patterns between treatment groups.Compare 12-month change in hip joint motion and moments in gait between treatment groups.Compare 12-month change in hip isometric muscle strength between treatment groups.Compare 12-month change in hip joint contact forces between treatment groups.

The objectives of the UK FASHIoN trial [25] are secondary objectives of our trial, and include:Compare changes in patient-reported hip-specific quality of life after 12 months, as measured by the international Hip Outcome Tool-33 (iHOT-33).Compare changes between treatment groups in general health status and health-related quality of life after 12 months, as measured by the Short Form-12 (SF-12).Compare differences between treatment groups in patient satisfaction with treatment and outcome after 12 months.Compare differences between treatment groups in the number and severity of adverse events after treatment after 12 months.Compare differences between treatment groups in the need for further surgical procedures up to three years.Compare the cost-effectiveness of hip arthroscopy for FAI with non-surgical care, within the trial, and estimated for a patient’s lifetime.Measure fidelity of delivery of interventions.

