### Adverse events

The number and type of adverse events will be recorded for all participants up to 12 months. Adverse events (AE) are defined as any untoward medical occurrence in a clinical trial patient and which do not necessarily have a causal relationship with the treatment. All AEs will be listed on the appropriate Case Report Form for routine return to the researchers. Serious adverse events (SAE) are defined as any untoward and unexpected medical occurrence that: results in death; is life-threatening; requires hospitalisation or prolongation of existing inpatients hospitalisation; results in persistent or significant disability or incapacity; is a congenital anomaly or birth defect; or any other important medical condition which, although not included in the above, may require medical or surgical intervention to prevent one of the outcomes listed. All SAEs will be reported to the ethics committee within 72 h of the investigators becoming aware of them. All participants experiencing SAEs will be followed-up as per protocol until the end of the trial.

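### The safety objective is to compare the number and severity of adverse events, but the stated data item is number and type and the stated test is yes/no

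*Protocol article*

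**What the plan says.** Three sections of the protocol article describe the adverse-event comparison.

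- **Secondary objectives**, in the list shared with the parallel UK trial: "Compare differences between treatment groups in the number and severity of adverse events after treatment after 12 months".
- **Adverse events**: "The number and type of adverse events will be recorded for all participants up to 12 months". The section adds "All AEs will be listed on the appropriate Case Report Form for routine return to the researchers". It then separates out serious events by their consequences: "Serious adverse events (SAE) are defined as any untoward and unexpected medical occurrence that: results in death; is life-threatening", followed by hospitalisation, disability and similar criteria. No severity grade is named.
- **Statistical analysis, Descriptive analysis**: the sentence on binary endpoints opens with "Differences in dichotomous outcome variables such as adverse events" and gives treatment complications and later procedures as its other examples. The method it assigns to all of them is a chi-squared test, or Fisher's exact test as the alternative. The same section promises standard summaries for all outcome measures and a graph of complications and further procedures over time. It names a proportional odds model for patient satisfaction only.

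**The concern.** The three sections should describe one chain: what is to be compared, what is recorded, and how it is tested. Here the chain breaks twice. Severity in the objective becomes type in the data item, and number in both of those becomes yes/no in the test. A participant with one trivial event and a participant with several severe ones count the same in the named test.

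The trial sets an operation against physiotherapy, so a reader will want to know the relative burden of harm as well as how many people had any event at all. Adverse events are defined broadly, whether or not treatment caused them, so having at least one in 12 months may be common in both arms. Severity is also best graded when the event is reported; grading later from type alone would be retrospective.

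**Working it through.** **1. The sections side by side**

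| Place | Number of events | Severity |
|---|---|---|
| Secondary objectives | to be compared | to be compared |
| Adverse events | recorded | not named; type is recorded, and serious events are defined |
| Descriptive analysis | reduced to yes/no | no comparison stated |

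The other methods in the analysis text do not fill the gaps. The t-test and covariance strategy is for approximately normal outcomes, proportional odds is named for satisfaction, and the graphs and Kaplan-Meier curves concern complications and further procedures. The serious/non-serious split is a classification by consequence. It is not a grade of severity, and its wording also requires the event to be unexpected, so an expected complication could fall outside it.

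**2. Does the yes/no test address number?**

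The article gives no adverse-event rate, so this is an illustration. Recruitment is 140 with 20% drop-out (Sample size section), so 140 × 0.8 / 2 = 56 per arm are analysed. Suppose 28 of 56 in each arm have at least one event, with one event each in one arm and two each in the other.

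- Event rates: 28/56 = 0.5 and 56/56 = 1.0 per participant, a rate ratio of 2.
- Yes/no table: 28 v 28 affected, 28 v 28 unaffected; chi-squared p = 1.0.

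The event rate doubles and the named test shows nothing, because it answers a different question.

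**3. How much power is at stake?**

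Assumptions, none from the article: negative binomial counts with shape 2 and the mean rates below. The probability of at least one event is 1 − (2/(2 + mean))². For example, at mean 1.5 it is 1 − (2/3.5)² = 0.67. The yes/no column is a two-proportion test. The rate column is a Wald test of the log rate ratio with empirical variance. Both are two-sided at 5%, with 20,000 simulated trials per row.

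| Mean events per participant | Any event | 70 per arm: yes/no | 70 per arm: rate ratio | 56 per arm: yes/no | 56 per arm: rate ratio |
|---|---|---|---|---|---|
| 0.1 v 0.25 | 9% v 21% | 49% | 52% | 41% | 42% |
| 0.2 v 0.4 | 17% v 31% | 46% | 52% | 38% | 43% |
| 0.7 v 1.2 | 45% v 61% | 47% | 71% | 38% | 61% |
| 1.5 v 2.5 | 67% v 80% | 42% | 85% | 34% | 76% |

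With equal means (1 v 1 and 2 v 2) both tests reject in about 5% of trials. Repeat runs move the powers by about one point; another run of the last row at 70 per arm gave 43% and 86%.

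The gain is a few points or less when events are rare and large when they are common. The simulation says nothing about severity.

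**The case against.** The strongest defence is that this is a condensed article. The case report form is not shown and may already hold a severity field, and count or worst-grade analyses are often left to a statistical analysis plan. The words introducing the dichotomous outcomes do not say that this is the only safety analysis. Comparing the proportion affected is standard safety reporting, and descriptive summaries are promised for all outcomes.

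Much of this stands, and it limits the point. A reader might infer that the safety objective cannot be answered, or that severity cannot be compared at all. The document does not support either reading: event counts are recorded and can be summarised and compared, the form's fields are unknown, and the serious/non-serious split gives a coarse related comparison. A reader might also infer that the yes/no outcome saturates, with nearly everyone having an event. The article gives no rate to support that, and even the higher assumed rates above leave 20% to 55% of an arm without an event.

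What does not stand is the claim that nothing is wrong in the text. The article is not silent: it states a data item and a test, and neither matches the objective. The phrase at issue lists examples of dichotomous variables and does not announce a further count analysis. Descriptive summaries do not supply a stated between-group comparison of counts or severity.

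**Conclusion.** The mismatch holds on the face of the article. Followed as written, the plan tests only the proportion of participants with an event. The number of events is recorded but has no stated comparison, and severity has neither a stated data item nor a stated comparison.

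The cost in power cannot be fixed from the document. Under the assumed counts it runs from close to nothing with rare events to roughly half the achievable power with common ones. The inconsistency itself does not depend on those assumptions.

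This is a minor point about one secondary objective. The primary dGEMRIC analysis and its sample size are unaffected, and safety oversight by the monitoring board and the reporting of serious events to the ethics committee run separately.

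**What to change.** - Keep the chi-squared or Fisher's exact test for any event and for serious events.
- Add a comparison of events per participant as a rate ratio with 95% CI, for example from a negative binomial model, using the counts already recorded.
- State that each event receives a defined severity grade, adding the field if the case report form does not already hold one. Compare the worst grade per participant, with no event as the lowest category, by the proportional odds model already planned for satisfaction.
- If severity will not be graded, reword the secondary objective to number and type, so that the three sections agree.

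The cost is about two lines of analysis text and at most one form field. The small downside is that sites must grade each event.

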### Need for further procedures

The need for any further treatments will be recorded for participants in both arms of the study. Further treatments may include but are not limited to hip arthroscopy, open hip preservation surgery, hip replacement, or additional non-protocol physiotherapy. The need for further procedures will be ascertained by questionnaire at two years and three years.

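### Kaplan-Meier is named for the cumulative incidence of a first procedure of a specific type, with no provision for procedures that preclude that event and no statement of which event is meant

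*Protocol article*

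**What the plan says.** The Statistical analysis section of the protocol article (under Descriptive analysis) plans, if events suffice, cumulative incidence curves of the "time to first procedure (any or a specific type) will be plotted by treatment group calculated using the Kaplan-Meier method". It names no other estimator, and it does not say how a participant who has a different procedure first is handled.

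The section Need for further procedures gives an open list of types: "Further treatments may include but are not limited to hip arthroscopy, open hip preservation surgery, hip replacement, or additional non-protocol physiotherapy". On timing it says: "The need for further procedures will be ascertained by questionnaire at two years and three years".

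The formal comparison is separate from the curves: "the need for further procedures will be compared between groups using chi-squared tests (or Fisher’s exact test"). The secondary objectives are narrower than the list of types, because they refer to further surgical procedures up to three years.

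**The concern.** One minus the Kaplan-Meier estimate equals the cumulative incidence only when every censored participant could still have the event later. That is acceptable for any procedure, where death is the only competing event and is rare in this young population.

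For a specific type it may not be acceptable. The phrase in the parenthesis can be read in two ways:

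- **Reading A, the type of the first procedure.** The types are mutually exclusive. A participant whose first procedure was another type can no longer have the event, and Kaplan-Meier can only censor that person as if still at risk.
- **Reading B, the first procedure of that type.** A participant who has had another type stays at risk, unless that procedure rules the event out. A hip replacement rules out later arthroscopy or joint-preserving surgery on the same hip.

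At stake is the accuracy of the type-specific three-year risks shown by arm. Under reading A with complete follow-up, the crude type-specific percentages equal the Aalen-Johansen estimate at three years. The Kaplan-Meier curve would end above the trial's own percentages, and by more in an arm with more competing procedures.

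**Working it through.** **Inputs.** The protocol gives no procedure rates, so there is no figure of its own to reproduce, and every rate below is an assumption. From the Sample size section: 140 participants and 20% drop-out, so 140/2 × 0.8 = 56 per arm. The horizon is three years and cause-specific hazards are taken as constant.

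**Reading A.** Let A be the true three-year incidence of the type as first procedure, and B that of all other first procedures.

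- Total cumulative hazard: L = −ln(1 − A − B)
- Type-specific share: a = L × A/(A + B)
- Kaplan-Meier reading: 1 − exp(−a)
- Standard error: √(A(1 − A)/56). For A = 20% this is √(0.16/56) = 5.35 points.

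Example with A = B = 20%: L = −ln(0.60) = 0.511; a = 0.511 × 0.5 = 0.255; 1 − exp(−0.255) = 22.5%. The excess is 2.5 points, or 2.54/5.35 = 0.48 standard errors.

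| Competing B | 1 − KM (true 20%) | Excess, points | Excess / SE |
|---|---|---|---|
| 5% | 20.6% | 0.6 | 0.10 |
| 10% | 21.2% | 1.2 | 0.22 |
| 20% | 22.5% | 2.5 | 0.48 |
| 30% | 24.2% | 4.2 | 0.79 |
| 40% | 26.3% | 6.3 | 1.18 |

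Under this reading the type curves should add up to the curve for any procedure. Take three types (arthroscopy, hip replacement, physiotherapy) with shares of 60/10/30%. Let P be the incidence of any procedure and H = −ln(1 − P), so that each curve reads 1 − exp(−H × share).

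| Any procedure (P) | Sum of the three Kaplan-Meier curves |
|---|---|
| 10% | 6.1 + 1.0 + 3.1 = 10.3% (from unrounded terms) |
| 30% | 19.3 + 3.5 + 10.1 = 32.9% |
| 50% | 34.0 + 6.7 + 18.8 = 59.5% |

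Aalen-Johansen curves sum exactly to P.

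**Reading B.** With the same hazards, a prior procedure of another type does not censor. Only hip replacement blocks a later arthroscopy. The true incidence of arthroscopy is then (0.6/0.7) × (1 − exp(−0.7H)). Kaplan-Meier with censoring at hip replacement reads 1 − exp(−0.6H).

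| P | H | True arthroscopy | Kaplan-Meier | Excess, points |
|---|---|---|---|---|
| 10% | 0.105 | 6.09% | 6.13% | 0.03 |
| 30% | 0.357 | 18.9% | 19.3% | 0.3 |
| 50% | 0.693 | 33.0% | 34.0% | 1.1 |

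Death aside, the hip-replacement and physiotherapy curves are not biased here. The true type-specific incidences sum to more than P, because one participant can have several types. At P = 30% they sum to 18.9 + 3.5 + 10.1 = 32.6% (from unrounded terms).

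**The case against.** A reader might infer something stronger: that Kaplan-Meier necessarily censors other first procedures, that every type-specific curve is therefore too high, and that curves adding up to more than the curve for any procedure prove the error. The documents do not support this. No censoring rule is stated, and reading B is as ordinary a reading as reading A. The list of treatments is open and says nothing about exclusivity. A participant can have physiotherapy, then arthroscopy, then a replacement. Under reading B most types are not precluded by the others, and a sum above the curve for any procedure is expected.

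The size is also open to challenge. A competing share of 20 to 40% is plausible mainly if non-protocol physiotherapy counts as a type. The protocol is mixed on this. Physiotherapy is in the list under Need for further procedures, but the secondary objective refers to surgical procedures, and physiotherapy beyond the study sessions is recorded as a co-intervention. The nearest figure in the document is the 5% crossover to surgery allowed for under Sample size, which is not a three-year procedure rate. At 5% competing events the excess is about a tenth of a standard error.

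The curves are also drawn only if events suffice, the arms are compared by chi-squared or Fisher's exact test, and the event definition for such a plot could be left to a statistical analysis plan.

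Most of this stands, and it limits both the claim and its weight. It does not remove the point. The protocol does not leave the estimator open: it names Kaplan-Meier for a quantity it calls cumulative incidence. Under either reading that is the wrong estimator for at least the types that a hip replacement precludes.

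**Conclusion.** The point holds as a minor improvement. Kaplan-Meier is right for any procedure. For a specific type it overstates the cumulative incidence wherever another procedure or death precludes the event, and the protocol makes no provision for that.

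- If the curve is for the type of the first procedure, the excess is negligible at about 5% competing events and about 2.5 points at 20% true and 20% competing incidence. It is larger if physiotherapy counts as a type and is common.
- If the curve is for the first procedure of that type, the excess is about 1 point or less in the scenarios computed and is confined to types that hip replacement or death precludes.

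These sizes rest on assumed rates, assumed shares and constant hazards. Neither the primary dGEMRIC analysis nor the planned test of further procedures is affected.

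**What to change.** In the Statistical analysis section:

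1. Keep Kaplan-Meier for the time to any first procedure.
2. State whether each type-specific curve is for the type of the first procedure or for the first procedure of that type.
3. Plot the Aalen-Johansen cumulative incidence by arm wherever another procedure or death precludes the event. Under the first definition the competing events are all other first procedures and death. Under the second they are hip replacement (for joint-preserving procedures on that hip) and death.

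The cost is a sentence or two and a different standard routine, with no new data or participants. The type-specific percentages will be slightly lower than those from Kaplan-Meier.
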